## 3.9 Sensitivity Analyses

The primary and secondary endpoints as well as the final models from the extended analyses will also be evaluated in the PP population, to investigate the sensitivity of the results. This sensitivity analysis will only be performed if the number of major protocol violations suggests that the main results may change.

The primary and secondary analyses will also be replicated using multiple imputation to assess the impact of the missing data values (where applicable).

In addition, sensitivity analyses will be performed on the secondary endpoints for the CV death ‘equivalent’ events - heart transplantation, appropriate shock from ICD, LTAD insertion and survived resuscitation of sudden cardiac arrest.

## 3.10 Missing Values

For the primary analysis no missing values will be replaced for the main analysis and so complete cases will be used (although there should be no missing values for the selected baseline covariates and the outcome is time to event, which allows for censored observations). Should there be any missing data then a supplementary sensitivity analysis that makes use of multiple imputation will be presented to assess the impact of the missing values.

For the secondary analyses complete case analyses will be used as the main analyses (although again the time to event outcomes allow for censored outcome data). In a similar fashion to the primary analysis multiple imputation will be used to assess the impact of any missing data as a supporting sensitivity analysis.

For the extended analyses multiple imputation will be used for the final models to assess the impact of any missing data on the conclusions.

## 3.11 Analysis Software

Data processing, elaboration, description and any additional coding or recoding, as well as all main analyses will be performed using the following routine licensed statistical software programmes:

1. SAS version 9.3 or later.
2. SPSS version 22 or later.
3. Stata version 12 or later.

All analyses and software scripts/logs will be stored in a shared directory on a secure server which can be accessed by the data manager, trial statistician and other study investigators.

# Section 4. Health Economics Analysis

## 4.1 Measurements and elaboration

The economic evaluation comprises a cost effectiveness analysis in terms of incremental cost per QALY. The composite nature of the primary outcome prevents its use as a measure of cost effectiveness. The perspective is that of the NHS.

In addition a process evaluation will compare the pattern of care between the two arms and across centres (usual care is not standardised and the protocol may be interpreted slightly differently by centre). Key abnormalities detected in remote monitoring relate to atrial/ventricular arrhythmias and HF events. Key interventions include changes in medication, including anti-coagulants for atrial fibrillation. Interventions in both groups will be assessed and compared.

.

## 4.2 Process evaluation

To the extent that remote monitoring in REM-HF leads to superior outcomes, it would do so by a process in which monitoring led to changes in treatment, mainly through medication changes (e.g., change in dose of diuretic, addition of new diuretic, anticoagulation for AF, etc.) and / or device re-setting. The process evaluation using data collected in the trial will measure the extent to which such changes in medication and in device re-sets occurred more frequently in the intervention compared to the control arm. The frequency of intervention by type would be compared with available data from other similar trials, with exploration, if relevant, of the implications for cost effectiveness.

## 4.3 QoL assessment

EQ5D data will be used with the UK tariff to estimate differences in QALY increments. Values will be interpolated between collection points and differences estimated using area under the curve.

### 4.3.1 Transformation of skewed data

Log-transformation or bootstrapping of any continuous data (e.g. direct costs), will be applied as required. If normality is not achieved, these data will be analysed by non-parametric analyses and tests.

The non-parametric method of bootstrapping, which makes no assumptions concerning the distribution of the underlying data will be applied to data on cost and quality of life.

### 4.3.2 Missing data

No imputation of missing data will be applied for the CEA data. Only patients with complete data will be included in the primary economic analysis, with imputation explored in sensitivity analyses.

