**7 Staffing of the Study and Study Grant Costs**:

Staffing and costs have been calculated on basis of a preliminary feasibility study that has demonstrated feasibility of study design and practicality of service delivery and that indicates expectation of patient compliance/acceptance. Industry charges for use of the remote monitoring technology will be already made by the healthcare services as remote device management is now common clinical practice. If that is not the case it is anticipated that industry partners will waive charges for the duration of the study although the notional cost will be included in the study analysis.

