## 4.4 Costs

The relevant costs are those of the intervention and of linked changes in the resources used related to HF. These include medications, devices, SAEs, any other HF related hospitalisations and use of community health services.

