### 4.4.1 Intervention cost

The intervention, remote monitoring, has to do with the provision of the monitors in each of the 9 sites. This excludes the cost of the devices fitted as these would be fitted anyhow. The direct cost of the remote monitoring will be personnel, seven of which were HF nurses (band 7) and two physiologists. These personnel worked partly on providing the intervention but also partly as researchers. Their research roles included recruitment, consent and data recording. Their remote monitoring role had to do with receiving and checking the weekly patient downloads and recommending changes as required. These elements have to be separated with only the costs of the intervention being relevant to the economic evaluation. The relevant cost is what the intervention might cost if applied in routine practice.

To separate these aspects, the relevant person at each centre was asked to identify the total time spent on REM and to divide this between that devoted to the intervention and that to do with the research, at the start and in early 2015. The time devoted to providing the intervention was aggregated by centre and multiplied by the staff cost, based on a HF nurse band 7 including overheads.

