### 4.4.2 Resource use data

Data relevant to the use of NHS resources were collected in five routine questionnaires headed:

1. Healthcare Utilisation Form,
2. System Modification,
3. SAE Hospitalisation,
4. Medication, and
5. Follow up interview.

These were administered at baseline, 3, 6 and 12 months and then yearly with the final collection at trial exit.

Levels of resource use by patient will be estimated under the following seven headings:

1. System modification (including reasons from a pre specified list)
2. CVD medication by 11 classes at start of study and new medication during the study with date. Other medication was recorded as yes/no.
3. Cardiac tests/procedures as day case admission
4. SAEs resulting in a hospitalisation, divided between those related to the study and not, along with duration of hospital stay
5. Hospital admissions (any other HF related hospitalisations other than SAEs)
6. Use of GP and practice nurses and Cardiac / HF Specialist nurses
7. Outpatient appointments and any A&E attendances.

Of these, 1) to 4) are plausibly related to the intervention while 5) to 7) refer to wider changes in health service use. For each of these items, the cost will be estimated as number of contacts multiplied by unit cost. The unit costs for GPs, practice nurses and Cardiac / HF nurses will be taken from PSSRU^5^. Hospital services costs, including for SAEs will be taken from National Reference costs. Drug costs by class will be taken from the BNF and PPA. The unit cost of system modifications will be based on that of an outpatient or day case contact as recorded in the trial. The cost of any A&E attendances will also be included.

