### 4.4.4 Cost Analysis

Costs will be estimated as the sum of the costs of the intervention, hospitalisations, and medication. They will be calculated by multiplying measures of resource use time estimates by unit costs for each type of resource^6-7^. The description of the services provided to the patients or the medical procedures used for the initiation of treatment or for use of the device will be provided by each centre.

The costing year will be the last study year prior to data unblinding (2014/2015) - if cost data are not available for this year, inflation of previous cost years data will be performed.

QALYs can be estimated from both EQ5D and SF12, both of which were administered at baseline, in addition to 12 and 24 months (or at trial exit if less than 24 months). The primary analysis will use EQ5D with the SF12 used in a sensitivity analysis.EQ5D will be used to estimate QALYs via the UK valuation set. Utility scores will then be multiplied by the duration of time spent in that health state and total QALYs will then be calculated with the area under the curve method.^8-12^

Both QALYs and intervention costs will be estimated at patient level once the final dataset is made available. This will enable both to be included in the statistical analyses described above. This will be done by the trial statistician or by the health economic team as appropriate.

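### The economic base case keeps only patients with complete data, without saying how death enters QALYs or costs, and the cost total in SAP 4.4.4 contradicts the wider cost definitions elsewhere

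*Combined protocol and SAP*

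**What the plan says.** **Population.** SAP 3.2.2 lists incremental cost per QALY as secondary endpoint 19. SAP 3.6 puts all secondary comparisons on the ITT population, which SAP 3.1.1 defines as everyone randomised. SAP 4.3.2 then says: "Only patients with complete data will be included in the primary economic analysis, with imputation explored in sensitivity analyses".

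**Utilities.** Protocol section 9 and SAP 2.4.1 collect EQ-5D at enrolment and at 3, 6, 12 and 24 months, by post after the first. SAP 4.3 interpolates between collection points and takes the area under the curve. SAP 4.4.4 says of EQ-5D and SF-12 that they are "both of which were administered at baseline, in addition to 12 and 24 months", or at trial exit if that is earlier. No section gives a utility after death.

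**Costs.** SAP 4.4.4 defines the total: "Costs will be estimated as the sum of the costs of the intervention, hospitalisations, and medication". SAP 4.4 says of the relevant costs: "These include medications, devices, SAEs, any other HF related hospitalisations and use of community health services". SAP 4.4.2 lists seven resource headings, among them "Use of GP and practice nurses and Cardiac / HF Specialist nurses", and adds: "For each of these items, the cost will be estimated as number of contacts multiplied by unit cost".

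**Technology charge.** Protocol section 7 expects health services to be paying the monitoring charges already. Where they are not, it expects industry to waive them, "although the notional cost will be included in the study analysis". SAP 4.4.1 says: "The direct cost of the remote monitoring will be personnel".

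**The concern.** Cost-effectiveness is part of the study hypothesis and of the first protocol objective. A complete-case ICER describes whoever meets the completeness rule, not the patients randomised. If that rule requires forms up to 24 months, nobody who dies earlier can meet it. Any survival difference between the arms would then leave the QALY comparison, and the costs those patients incurred up to death would leave with it.

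The cost total matters because of where the pathway sends its work. Section 2 of the monitoring handbook (Appendix II) routes drug changes and blood tests through the GP or community heart failure nurse, and specialist tests and reprogramming through the local centre. Several of these contacts fall under headings that the three-item sum omits. Two analysts following different sections of the same SAP would reach different totals.

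**Working it through.** **1. Size of the death question.** The documents give no mortality rate for this trial, so the inputs are partly assumed:
- Two-year usual-care mortality d: 5% to 25% (assumption). That is 0.05 × 825 = 41 to 0.25 × 825 = 206 deaths per 825 patients.
- Mortality ratio r, applied as a hazard ratio: 0.83, the pooled relative risk of death in the randomised trials cited in the protocol Background, and 0.80 as a slightly larger assumed effect.
- Utility while alive: 0.55 (Appendix I). Utility after death: 0.

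With exponential survival, the hazard is h = −ln(1 − d)/2 and life-years over two years are (1 − exp(−2h))/h. The QALY difference is 0.55 × [life-years at r × h − life-years at h].
- d = 0.05, r = 0.83: h = 0.0256; life-years 1.950 and 1.958; difference 0.0046 QALY.
- d = 0.25, r = 0.80: h = 0.1438; life-years 1.738 and 1.787; difference 0.0267 QALY.

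The range is about 0.005 to 0.027 QALY over two years. An analysis of two-year survivors shows none of it. Appendix I's smaller scenario is 0.02 QALY for one year. Halved to a yearly figure, the range is 0.0023 to 0.013, roughly one-eighth to two-thirds of that gain.

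**2. The definition of complete decides who is counted.** Assume 85% to 95% return of each postal form, independently. If all four are required, 0.85⁴ = 52% to 0.95⁴ = 81% of survivors are complete. If only 12 and 24 months are required, it is 0.85² = 72% to 0.95² = 90%. Positively correlated returns would raise these figures. The SAP does not say which rule applies.

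**3. The cost statements side by side.**
- SAP 4.4.4: intervention, hospitalisations, medication.
- SAP 4.4: also devices and community services.
- SAP 4.4.2: all seven headings priced, including system modifications, day-case tests, GP and nurse contacts, outpatient visits and A&E.
- SAP 4.4.3: system modifications costed as attendances.
- SAP 4.4.5: base case uses NHS costs related to heart failure.
- Protocol section 10: all heart-failure-related care costs in both arms.

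The first cannot be reconciled with the rest.

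**4. Size of the cost question.** The Appendix I scoping total reproduces exactly: 289 (medicines) + 52 (GP) + 7 (practice nurse) + 89 (outpatient) + 771 (inpatient) = £1,208 per patient-year. The narrow sum covers 289 + 771 = £1,060 (87.7%). The rest is 52 + 7 + 89 = £148 (12.3%). These are levels; only a difference between arms moves the ICER. At a gain of 0.02 QALY, each £10 per patient-year of between-arm difference left out shifts the result by 10/0.02 = £500 per QALY.

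**The case against.** A reader might infer that patients who die are excluded. No section says so. SAP 4.4.4 allows a final utility at trial exit and multiplies utility by time in state, so a record ending in death could be treated as complete. That rebuts a claim of settled exclusion. It does not fill the gap: a questionnaire at exit cannot be completed by someone who has died, and no rule supplies a value.

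A reader might also infer that community and outpatient care is left out of the ICER. SAP 4.4, 4.4.2, 4.4.3 and 4.4.5 plan to cost it, and monitor time spent starting interventions counts as intervention cost in the staff survey (SAP 7.6.1). The documents support an unreconciled conflict, not an omission.

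SAP 3.6 refers the health economics methods to Section 4, so 4.3.2 may be meant as the specific rule, and it plans imputation as a sensitivity analysis. That is fair, but the same SAP section puts all secondary comparisons on the ITT population, and the headline ICER would still be the complete-case one.

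Two smaller points shrink on inspection. The technology charge is conditional, and protocol section 9 notes that remote device follow-up is already usual in many centres, so a charge borne by both arms is not incremental. The EQ-5D schedule in SAP 4.4.4 does not say that the 3- and 6-month forms are discarded, and SAP 4.3 interpolates between collection points; this is a matter of wording.

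The scoping costs come from a 2003/4 cohort in which ICDs were probably uncommon, so the 12.3% may not carry over to this trial.

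**Conclusion.** The concern holds in a limited form. The base case is explicitly complete-case, complete data are undefined, the treatment of death is unstated, and the cost total in SAP 4.4.4 contradicts the rest of the plan. The death question could be worth about 0.005 to 0.027 QALY over two years, given the assumed mortality and ratio, exponential survival and a utility of 0.55. The headings in dispute are £148 of £1,208 on the scoping figures.

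It would be tempting to conclude that the plan favours remote monitoring. The documents do not show that. Losing a survival gain would count against it. Losing community contacts could favour it, but the protocol's statement of originality expects less face-to-face secondary and tertiary contact, so omitting outpatient costs could work the other way. Nor does the survival component equal Appendix I's whole gain: the former accrues over two years, the latter in one.

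This should be fixed before the data are analysed. It concerns a secondary endpoint and leaves the primary analysis untouched.

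**What to change.** - **Population:** make all randomised patients the base case in SAP 4.3.2, with EQ-5D set to 0 from the date of death, costs counted to death, and multiple imputation by arm for missing EQ-5D and resource use. Keep complete-case as the sensitivity analysis and define complete for it.
- **Cost total:** rewrite SAP 4.4.4 as the intervention plus all seven headings of SAP 4.4.2.
- **EQ-5D:** state that all five time points enter the area under the curve.
- **Technology charge:** include the notional charge only where the condition in protocol section 7 applies and the charge is incremental to usual care, or state that the increment is nil.

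The cost is SAP wording and an imputation model on data already collected, so a little more analysis work. The ICER may move in either direction.

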## 4.4 Costs

The relevant costs are those of the intervention and of linked changes in the resources used related to HF. These include medications, devices, SAEs, any other HF related hospitalisations and use of community health services.

### 4.4.1 Intervention cost

The intervention, remote monitoring, has to do with the provision of the monitors in each of the 9 sites. This excludes the cost of the devices fitted as these would be fitted anyhow. The direct cost of the remote monitoring will be personnel, seven of which were HF nurses (band 7) and two physiologists. These personnel worked partly on providing the intervention but also partly as researchers. Their research roles included recruitment, consent and data recording. Their remote monitoring role had to do with receiving and checking the weekly patient downloads and recommending changes as required. These elements have to be separated with only the costs of the intervention being relevant to the economic evaluation. The relevant cost is what the intervention might cost if applied in routine practice.

To separate these aspects, the relevant person at each centre was asked to identify the total time spent on REM and to divide this between that devoted to the intervention and that to do with the research, at the start and in early 2015. The time devoted to providing the intervention was aggregated by centre and multiplied by the staff cost, based on a HF nurse band 7 including overheads.

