**12 Training**

*Remote Monitoring Preparation*

Patients will be introduced to the remote monitor providing remote care and will be instructed in use of the care pathways.

Patients will receive training on use of remote monitoring through their implanted device by the study site remote monitor. They will receive their home monitoring transmission devices (specific model depending on implant device features). Devices will be interrogated using a monitor with automatic or manual download capabilities with either wireless or non wireless technology.

The remote monitor will communicate with the patients’ primary care services to inform them of entry to the study

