## 7.5 Trial Timeline

## 7.6 Health economics: questionnaire and results (RMS)

### 7.6.1 Questionnaire sent to RMS

Please estimate the average number of hours per week the remote monitor role at your site is spending in each of the following three activity groups, both during the first year if you were employed at that time and again now. Please put a whole number in here not a range. It is just your estimate.

| **Site name:** | **Year 1** | **Year 3** |
| --- | --- | --- |
| **Download specific:**  *Reviewing the downloads*  *Initiating interventions as a result of the downloads* |  |  |
| **Research Specific Activity:**  *Screening patients*  *Randomisation and baseline visits*  *Research paperwork- GP information sheets, health questionnaires*  *ECRF data entry*  *Reporting SAEs and collecting source data*  *Follow up visits* |  |  |
| **Other:**  Any other activity or tasks such as other duties/mandatory training /meetings etc |  |  |

Thank you for completing this.

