### 7.6.2 Results of RMS survey

| Year 1 | Newcastle | Guys | Liverpool | Blackpool | Leicester | Leeds | Soothampton | Brompton | Manchester |  |  |
| --- | --- | --- | --- | --- | --- | --- | --- | --- | --- | --- | --- |
| Monitoring | 18 | - | 12 | 14 | 10 | 12 | 6 | 10 | - | 12 | 31 |
| Research | 18 | - | 25 | 20 | 28 | 35 | 25 | 12 | - | 23 |  |
| Other | 2 | - | 1 | 3 | 5 | 2 | 4 | 1 | - | 2 |  |
| total | 38 |  | 38 | 37 | 43 | 48 | 35 | 23 |  | 37 |  |
| Year 2 |  |  |  |  |  |  |  |  |  |  |  |
| Monitoring | 12 | 22 | 10 | 10 | 15 | 17 | 12 | 6 | 10 | 13 | 39 |
| Research | 18 | 15 | 27 | 22 | 21 | 16 | 20 | 5 | 15 | 18 |  |
| Other | 2 | 1 | 1 | 5 | 2 | 1 | 4 | 1 | 3 | 2 |  |
| total | 32 | 38 | 38 | 37 | 38 | 33 | 36 | 12 | 28 | 32 | 39 |

Of the 9 centres, 7 replied for year one, and all in year two. These replies put the mean number of hours in year one at 37, with 12 devoted to monitoring. Figures for year two were 32 and 13 hours per week, respectively.

For costing, the mean number of hours per week in each centre devoted to monitoring will be 12 in year one and 13 in year two.

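### The base-case cost of remote monitoring is staff time only, with no place for the technology cost that the protocol conditionally promised; the hours also rest on a mislabelled survey point and an undefined divisor

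*Combined protocol and SAP*

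**What the plan says.** **Technology.** SAP 4.4.1 defines the intervention cost as staff: "The direct cost of the remote monitoring will be personnel, seven of which were HF nurses (band 7) and two physiologists". It leaves out implanted devices: "This excludes the cost of the devices fitted as these would be fitted anyhow". The same section says that the relevant figure is the cost the service would have in routine use.

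Protocol section 7 starts from the presumption that the health service already pays the industry charges for remote monitoring. If it does not, industry is expected to waive them, "although the notional cost will be included in the study analysis". Protocol section 12 says of patients being prepared for monitoring: "They will receive their home monitoring transmission devices".

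**Staff time.** SAP 4.4.1 says that staff were asked to split their hours "at the start and in early 2015". The form in SAP 7.6.1 has columns headed Year 1 and Year 3 and asks for hours "both during the first year if you were employed at that time and again now". The results in SAP 7.6.2 head the second block Year 2, and the costing rule reads: "the mean number of hours per week in each centre devoted to monitoring will be 12 in year one and 13 in year two".

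**Conversion to cost.** SAP 4.4.1 uses a staff rate that has overhead costs in it: "The time devoted to providing the intervention was aggregated by centre and multiplied by the staff cost, based on a HF nurse band 7 including" (the quote stops one word short of the end of the sentence). SAP 4.4.4 says that intervention costs will be estimated for each patient. SAP 4.4.5 plans sensitivity analyses on monitoring cost at different caseloads.

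**The concern.** Cost-effectiveness is in the protocol's objectives and in the study hypothesis, and SAP 4.4.5 will judge the result against £20,000 to £30,000 per QALY. Three things in the intervention cost need attention.

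1. A cost that the protocol says will be counted in some circumstances has no line in the SAP. Leaving it out can only lower the cost of the remote care pathway (RCP). Where a charge was waived for the trial, leaving it out also misses the SAP's own target of routine-practice cost, because a waiver is not routine practice.
2. The hours assigned to year two were collected for a later period.
3. The SAP has hours per centre and wants cost per patient, but gives no divisor. Two analysts could follow the text and reach different base-case costs.

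**Working it through.** **Is there a place for the technology cost?** The SAP's headings, in order:

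| SAP section | What it costs | Service charge or transmitter? |
| --- | --- | --- |
| 4.4 | Names devices among the relevant costs | Not itemised; 4.4.1 then excludes the fitted devices |
| 4.4.1 | Personnel | No |
| 4.4.2 | System modifications, CVD drugs, day-case tests, SAE admissions, other HF admissions, GP and nurse contacts, outpatient and A&E visits | No |
| 4.4.3 | Drugs, system modifications as attendances, SAE bed days | No |
| 4.4.4 | Sum of intervention, hospitalisation and medication costs | No |

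Followed as written, the SAP drops the notional cost even where the protocol's condition is met. The condition may well be met at some centres: Protocol section 9 says that remote technical follow-up is current practice in many centres, and does not say all.

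**Size of the omission.** Let c be the charge per patient-year, f the share of RCP patients for whom it is additional to usual care, and q the QALY gain per year. The ICER is understated by f × c / q, for q above zero.

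- q = 0.02 or 0.05: scoping values in Protocol Appendix I.
- c and f: not in the documents. I use c = £100 as a unit; f can lie anywhere from 0 to 1.
- f = 1: 100 / 0.02 = £5,000 per QALY; 100 / 0.05 = £2,000.
- f = 0.5: £2,500 and £1,000.
- f = 0: nothing is missing.

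**Survey hours, from the table in SAP 7.6.2.**

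- Year one, seven centres: (18 + 12 + 14 + 10 + 12 + 6 + 10) / 7 = 82 / 7 = 11.7, printed as 12.
- Second point, nine centres: (12 + 22 + 10 + 10 + 15 + 17 + 12 + 6 + 10) / 9 = 114 / 9 = 12.7, printed as 13.

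Both printed figures reproduce. The two centres with no year-one reply gave 22 and 10 h. Without them the second point is (114 − 32) / 7 = 82 / 7 = 11.7 h, the same as year one. The rise from 12 to 13 h therefore comes only from those two centres.

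**Survey date.** Recruitment began in September 2011 (SAP 1.2.2). January 2015 is 40 months later, in the fourth 12-month period. On neither that count nor the form's own heading is it year two.

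**Does the divisor matter?** This is an illustration, with these assumptions:

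- £60,000 per whole-time nurse (Appendix I);
- a 37.5-hour week (my assumption);
- 825 RCP patients in 9 centres;
- even recruitment over months 2 to 24 (my reading of a broken timetable in Protocol section 13);
- no attrition.

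Total staff cost per year:

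- 12 h: 9 × 12 / 37.5 × 60,000 = £172,800
- 13 h: 9 × 13 / 37.5 × 60,000 = £187,200

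Mean caseload, as a fraction of 825:

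- Year one: [10² / (2 × 22)] / 12 = 0.189, or about 156 patients
- Year two: [(22² − 10²) / (2 × 22)] / 12 = 0.727, or about 600 patients

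| Hours | Divided by 825 | Divided by mean caseload that year |
| --- | --- | --- |
| 12 h (year one) | £209 | £1,106 |
| 13 h (as year two) | £227 | £312 |

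The SAP does not say which column, or what other method, applies.

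**The case against.** The strongest reply concerns the technology charge. The protocol's default is that the health service already pays. Where that holds, the extra charge may be zero and a personnel-only cost is right. SAP 1.1 presents the SAP as further specification, and nothing in it withdraws the notional cost. This stands as a limit: a reader might infer that the protocol promised the charge for every RCP patient, and it did not. It does not remove the gap, because the SAP neither says which case arose nor gives the cost a heading.

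A reader might also infer that the SAP applies trial-year hours as if they were patient-years. The documents do not show this. The conversion is an unspecified step, not a stated misuse, and the caseload sensitivity analysis in SAP 4.4.5 covers part of the uncertainty. It varies the base case without defining it, and it does not touch the technology cost or the survey label.

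Nor is the absence of hours beyond year two a clear fault. SAP 3.2.2 sets a two-year window for secondary endpoints unless otherwise stated, and SAP 4.4.4 takes QALYs from questionnaires up to 24 months.

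Finally, the label itself moves little money. On a fixed 825 patients, 13 h in place of 12 h is £227 − £209, about £17 per patient-year before rounding. That is fair. The mislabel is a factual error to correct, not a driver of the result.

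**Conclusion.** The point holds in three parts of unequal weight.

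- **Technology cost omitted.** This matters most. The base-case ICER is too favourable to RCP wherever the charge is additional to usual device care. The size is £5,000 or £2,000 per QALY for each £100 per patient-year, at gains of 0.02 or 0.05, if all RCP patients are affected, and proportionately less otherwise. The charge and the share affected are unknown. The gains are scoping assumptions, set beside cost data that Appendix I says are for a non-ICD population. If the observed QALY gain is zero or negative, the omission still understates incremental cost by f × c.
- **Survey point mislabelled.** This is certain. Year two was not surveyed, and the rise in hours reflects which centres replied. The numerical effect is small.
- **Divisor undefined.** This is a gap in specification. The illustration shows that it could be large in year one, but the figures rest on the assumptions listed.

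The documents do not support a claim that the whole intervention cost is biased in one direction. Only the technology part has a known sign.

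**What to change.** (a) In SAP 4.4.1, add the notional annual service charge and the transmitter cost for RCP patients at centres where usual device care does not already incur them. Decide this centre by centre and use list prices. Add a sensitivity analysis that charges all RCP patients.

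(b) In SAP 7.6.2, relabel the second survey block as early 2015 (Year 3 on the form) and correct the costing rule to match.

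(c) For each centre, divide the early-2015 monitoring hours by the number of RCP patients under active monitoring there at that date, giving hours per patient-week. Apply this to each RCP patient's monitored weeks within the two-year horizon, and state that horizon. Use the year-one hours as a sensitivity analysis.

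The cost is SAP wording, a list price for each manufacturer, one determination per centre, and counts of active patients. The counts should be obtainable, since the 75% rule in SAP 3.1.2 already needs download records for each RCP patient. The downside is that adding the technology cost makes RCP look less favourable; the net direction of the staff-time change is unknown.
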